### Analysis plan

#### Primary outcomes

The primary outcomes are experiences, concerns, expectations and preferences around dying and end-of-life care of patients in the last phase of life and their relatives, at baseline and after 4 weeks follow-up, and will be described in frequencies and narrative descriptions. The proportion of patients who have certain concerns, expectations and preferences will be described. Subgroup analyses will be performed to assess cross-gender, cross-age and cross-cultural variety on experiences, concerns, expectations and preferences. Narrative descriptions will be translated into English and categorised into themes that will be identified within the data.

Descriptive statistics will be used to summarise baseline characteristics of the study participants (age, gender, education, diagnosis, comorbidities, religion, socioeconomic status, marital status, place of residence, quality of life, symptom load) by country and site. Statistics on mean/median scores and variance will be presented where applicable. Associations with country and patient characteristics will be analysed in a multilevel modelling approach, taking account of clustering effects at country level. Both univariable and multivariable analyses will be performed. All statistical tests will be two-sided and considered significant if p<0.05. Repeated measures analyses of variance will be conducted to assess the development of outcomes between baseline and 4 weeks follow-up. Multivariate Imputation by Chained Equations (MICE) will be used to handle missing data,^33^ as we expect that patients may not be able or want to fill in all questions in the questionnaire. MICE is known to be a flexible principled method of addressing missing data and can handle variables of varying types (eg, continuous or binary). Quantitative analyses will be performed with SPSS V.25.0 statistical software.

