**Methods and analysis:**

The iLIVE study is an international cohort study in which patients with an estimated life expectancy of 6 months or less are followed up until they die. In total, 2200 patients will be included in 11 countries, that is, 200 per country. In addition, one relative per patient is invited to participate. All participants will be asked to fill in a questionnaire, at baseline and after 4 weeks. If a patient dies within 6 months of follow-up, the relative will be asked to fill in a post-bereavement questionnaire. Healthcare use in the last week of life will be evaluated as well; healthcare staff who attended the patient will be asked to fill in a brief questionnaire to evaluate the care that was provided. Qualitative interviews will be conducted with patients, relatives and healthcare professionals in all countries to gain more in-depth insights.

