## Methods and analysis

### Study design and setting

The iLIVE study is a prospective observational cohort study involving terminally ill patients in hospital and non-hospital sites in 11 participating countries: Argentina, Germany, Iceland, the Netherlands, New Zealand, Norway, Slovenia, Sweden, Switzerland, Spain and the United Kingdom (UK). Countries from three continents over the world were included in the study to ensure cultural diversity within the study population. Terminally ill patients will be followed until they die or for a maximum of 6 months after inclusion. Participating patients and one of their relatives will complete questionnaires about their experiences, concerns, expectations and preferences around dying and use of end-of-life care. This 4-year study started in September 2020 and is currently ongoing.

In order to have a diverse study population regarding clinical and sociodemographic characteristics, we will recruit participants from different types of clinical settings. Patients will be recruited in the 11 participating countries, from a total of 20 hospitals (oncology, internal medicine, surgery, palliative care unit, medical physics, thoracic medicine and pulmonology departments), 7 specialised palliative care institutes and 8 out-of-hospital settings (nursing homes).

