### Sample size

The primary outcomes are measured at baseline and 4 weeks post-inclusion. It is expected that 30% of all patients who complete the baseline assessment will be lost to follow-up, due to death, significant deterioration of health or other causes. In that case, 70% of patients who complete the baseline measurement will be able to complete the assessment after 4 weeks at follow-up 1. Further, it is expected that 80% of all patients who complete the baseline assessment can be followed until death, whereas the remaining 20% are expected to either survive until the end of the data collection period or become lost to follow-up. Regarding the relatives, it is expected that in case patients who complete the baseline assessment die during follow-up, half of the bereaved relatives (ie, 40% of all baseline patients), will be willing to complete a post-bereavement questionnaire (follow-up 2). The total cohort would thus include 2200 patients (n=200 per country) at baseline, 1540 patients (n=140 per country) at follow-up assessment 1 and 880 bereaved relatives (n=80 per country). The number of 200 patients per country enables us to estimate proportions with 95% Confidence Intervals (CIs) of approximately ±7%. The number of recruiting sites will vary from two to six per country.

No sample size estimation has been performed for the qualitative interviews since the aim is to explore and better understand the variety in experiences of patients, relatives and physicians, rather than having a representative sample per country.

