#### Secondary outcomes

Secondary outcomes for patients include symptom load, health-related quality of life (HRQoL) and well-being, and attitudes towards physician assistance in dying. Secondary outcomes for relatives include HRQoL, well-being, informal care provision, attitudes towards physician assistance in dying and bereavement. The prevalence of these outcomes will be described in frequencies, mean/median scores and variance. Associations with country and patient characteristics will be analysed in a multilevel modelling approach, taking account of clustering effects at country level. Both univariable and multivariable analyses will be performed. Repeated measures analyses of variance will be conducted to assess the development of outcomes between baseline and 4 weeks follow-up. The relationship of the relative to the patient will be taken into account in multivariable models, in addition to the characteristics mentioned for the analysis of the primary outcome.

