## Discussion

The iLIVE study has several strengths. Going through the last phase of life is a complex personal experience, which is best understood while acknowledging the diverse and dynamic preferences of patients and their families. Due to the international nature of this project, we are able to investigate end-of-life experiences across different cultures and among groups varying by age, gender, illness and care setting. Further, we combine the perspectives of the most relevant stakeholders, that is, patients who are in the last phase of life and their relatives, as well as healthcare staff providing end-of-life care. Furthermore, patients and relatives will complete questionnaires at multiple time points, which enables us to analyse potential adaptations within subjects over time. Another strength relates to the post-bereavement assessment among relatives, which provides insights in the experience of care in the dying phase as well as the impact of these experiences on relatives’ well-being and bereavement after the death of a patient. Lastly, the study population is relatively large which enables us to perform subgroup analyses.

We expect to encounter several challenges in this study. Recruiting patients in the last phase of life for research studies is often difficult. For instance, healthcare professionals or family members may be hesitant to provide researchers’ access to incurably ill patients, due to concerns about burdening or distressing them, a phenomenon referred to as ‘gatekeeping’.^43^ In many studies, this has led to considerably smaller study samples than desired. To minimise this risk, we have involved multiple clinical sites in almost all participating countries, planned for modest numbers of participants per site and applied conservative estimates of expected dropout. In addition, we will screen all potentially eligible patients and keep track of inclusion and exclusion numbers, as well as reasons for non-participation or exclusion.

Another challenge is that persons at the end of life may not be able to complete the follow-up questionnaire as they may become weaker over time. This will be monitored during the study and necessary actions will be taken in order to improve completion of the follow-up questionnaire.

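### The multilevel model names country as its only cluster level, although country is also a factor under study, and does not mention recruiting site

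*Protocol article*

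**What the plan says.** The analysis plan's subsection on primary outcomes states: "Associations with country and patient characteristics will be analysed in a multilevel modelling approach, taking account of clustering effects at country level". The subsection on secondary outcomes repeats the clause: "taking account of clustering effects at country level". Inference is set by one rule: "All statistical tests will be two-sided and considered significant if p<0.05".

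Site enters the analysis plan only as a stratifier of the baseline descriptive tables, which are to be given by country and site.

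The section on study design and setting lists 20 hospitals plus "7 specialised palliative care institutes and 8 out-of-hospital settings (nursing homes"), which is 20 + 7 + 8 = 35 sites of mixed type. The sample size section adds: "The number of recruiting sites will vary from two to six per country". It also gives the precision per country: "The number of 200 patients per country enables us to estimate proportions with 95% Confidence Intervals (CIs) of approximately ±7" per cent. The Discussion says: "we have involved multiple clinical sites in almost all participating countries".

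The Introduction makes variability by culture part of the study's second aim, and the analysis plan carries this out through country.

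**The concern.** Patients are sampled within sites, and sites lie within countries. Patients at one site share staff, referral routes and type of setting, so their answers may be correlated. A country mean built from two to six sites then carries site-to-site noise that does not shrink as more patients are recruited at the same sites.

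The one cluster level named does not deal with this when the question is about country:

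- **Country as a fixed effect.** A country random intercept on top of 11 country terms adds nothing identifiable. The residual treats all patients in a country as independent, so standard errors for country contrasts are too small if site correlation exists.
- **Country as a random effect only.** Part of the site variance is read as variance between countries.

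At stake is the cross-country part of the second aim. With tests judged at p<0.05, differences between countries would be found falsely more often than 5% of the time.

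**Working it through.** **Inputs from the article.** 2200 patients, 11 countries, 200 per country; 35 sites, so 35/11 ≈ 3.2 per country on average; two to six sites per country; two-sided 5% tests.

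**Assumptions, not in the article.** Site ICC of 0.01, 0.02 or 0.05; sites of equal or near-equal size within a country; no true country difference; no covariate adjustment.

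**Step 1. The plan's own figure.** The half-width at a proportion of 0.5 is 1.96 × √(0.25/200) = 0.0693, which matches the stated ±7%. The formula treats the 200 patients as independent, with no allowance for site.

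**Step 2. Design effect.** DE = 1 + (m − 1) × ICC, with m = 200/k patients per site. At k = 3.2, m = 62.5:
- ICC 0.01: 1 + 61.5 × 0.01 = 1.615
- ICC 0.02: 1 + 61.5 × 0.02 = 2.23
- ICC 0.05: 1 + 61.5 × 0.05 = 4.075

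**Step 3. Two-country comparison that ignores site.** Actual type I error = 2 × [1 − Φ(1.96/√DE)]. At ICC 0.02 and k = 3.2, 1.96/√2.23 = 1.31, which gives 19%. At the extremes, six sites with ICC 0.01 (m = 33.3, DE = 1.32) give 8.8%, and two sites with ICC 0.05 (m = 100, DE = 5.95) give 42.2%.

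**Step 4. Test across all 11 countries that ignores site.** Two simulations were run with 4000 data sets per ICC and 35 sites. (a) A chi-square test on a binary outcome with an assumed prevalence of 40% and two to five sites per country. (b) A one-way F-test on a continuous outcome with two to six sites per country.

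| Assumed site ICC | Two-country error, 3.2 sites | Two-country error, six to two sites | 11-country error, (a) / (b) |
|---|---|---|---|
| 0.01 | 12% | 8.8% to 16.5% | 36% / 40% |
| 0.02 | 19% | 12.7% to 25.6% | 66% / 67% |
| 0.05 | 33% | 22.6% to 42.2% | 94% / 95% |

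With an ICC of about zero, simulation (a) rejects in 4.95% of runs, as it should. In the data of simulation (b), an F-test on site means rejects in 3% to 4% of runs, so the excess comes from ignoring site.

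**Step 5. Country as a random effect only.** Two patients in the same country share a site with probability about 1/k, so site variation alone yields an apparent country ICC of about ICC/k. With three sites this is 0.0033, 0.0067 and 0.017 at site ICCs of 0.01, 0.02 and 0.05. No rejection rate was computed for this reading.

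**The case against.** The best defence is that the article is silent on site and does not exclude it. It promises a multilevel approach, site is already recorded, and the full random-effect structure is often left to an analysis plan that is not shown here. That plan may well contain a site level. This stands as a limit on what can be claimed: a reader might infer that the investigators decided to leave site out, and the text does not show that. It does not remove the point, because the article chooses to name a cluster level, does so twice, and names one that gives country comparisons no protection.

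The size is also open to challenge. The ICC and the 40% prevalence are assumptions. The 11-country rates come from unadjusted tests, not from the planned model, and correspond to the fixed-country reading only. Multivariable models are planned, and sites probably differ in part by case mix, so the residual site ICC may be lower after adjustment. All of this stands.

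Three stronger inferences are not supported:
- *All site variation becomes country difference.* Only about 1/k of the site variance reaches the country means; the rest goes into the within-country residual.
- *Standard errors for care-setting factors are too small.* Care setting appears in the hypothesis, but the article specifies no setting-level model term, so there is nothing definite to criticise.
- *Some country has a single site.* The Discussion's wording permits this, but the sample size section gives at least two sites in every country, and no single-site country is identified.

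**Conclusion.** The point holds as a fault in a stated rule. The only cluster level named is country, which is also a factor to be estimated, and a model built as written does not account for correlation within sites.

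If the site ICC lies between 0.01 and 0.05 and countries do not truly differ, a two-country comparison has a false-positive rate of about 12% to 33% at the average of 3.2 sites per country, and about 9% to 42% over the range from six to two sites. The unadjusted 11-country test reaches about 36% to 95%. These rates depend on an ICC that the article does not give, and case-mix adjustment may lower them.

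A reader might conclude that countries differing by chance in their sites will be declared culturally different. The figures show only that this would happen too often, not that it would always happen.

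This is a should-fix matter. The primary outcomes are mainly described by frequencies and narrative, country comparison serves the second aim, and the model can be corrected at analysis without new data.

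**What to change.** In both outcome subsections, state that patients are modelled within sites within countries, with:
- a random intercept for site;
- country as a fixed effect with 11 levels where countries are compared;
- random intercepts for both site and country where the variance between countries is reported;
- small-sample degrees of freedom based on the number of sites (with 35 sites and 11 countries, about 35 − 11 = 24 for country contrasts).

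As a minor point, reconcile the sample size section's two to six sites per country with the Discussion's statement that nearly all countries have several. If any country does have a single site, say that its country effect cannot be separated from its site effect.

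The text change is a sentence or two. Site is already recorded, so no data collection changes. The cost is wider intervals for country comparisons.

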### Measurements

The iLIVE cohort study includes several measurements (table 2):

Questionnaires. Patients, relatives and attending physicians are asked to fill in questionnaires. Patients and relatives will complete questionnaires on enrolment in the study (baseline assessment) and 4 weeks later (follow-up 1). For patients who die during the follow-up period of 6 months, relatives will also complete a questionnaire 8–10 weeks after the death of the patient (follow-up 2). Questionnaires for patients and relatives are administered on paper, online or through telephone or face-to-face interviews. Physicians will complete a paper questionnaire at patient enrolment (baseline assessment) and after the death of a patient (follow-up 2).

**Table 2 T2:** Measurements among patients, relatives and physicians within the iLIVE project

I. Measured by questionnaire	Measurement instrument
Patients	
Concerns, expectations and preferences of patients around dying and end-of-life care	Self-developed questions adapted from the Serious Illness Conversation Guide^44^ and the AEOLI questionnaire^45^
Symptom load	Edmonton Symptom Assessment System (ESAS)^46^
Health-related quality of life (HRQoL) and well-being	EORTC QLQ-C15-PAL quality of life question^47^ and EuroQol 5 Dimension questionnaire (EQ-5D-5L)^48^ ICECAP Supportive Care Measure (ICECAP-SCM)^49^
Attitudes towards euthanasia*	10-item Euthanasia scale^50^
Health and social care resource use, absenteeism from work	(Partial) Health Economics Questionnaire (HEQ)^51^
Sociodemographic characteristics	Self-developed questions and HEQ
Relatives	
Concerns, expectations and preferences around dying and end-of-life care	Self-developed questions inspired by the Serious Illness Conversation Guide and the AEOLI questionnaire
Health-related quality of life (HRQoL)	EORTC QLQ-C15-PAL and EQ-5D-5L
Well-being	ICECAP Close Person Questionnaire (ICECAP-CPM)^52^
Informal care provision	iMTA Valuation of Informal Care Questionnaire (iVICQ)^53^ and Informal Care Cost Assessment Questionnaire (CIIQ)^54^
Attitudes towards euthanasia	10-item Euthanasia scale
Bereavement	Hogan Grief Reaction Checklist (HGRC, despair and personal growth subscales)^55^
Quality of care for dying patients	International questionnaire Care of the Dying Evaluation (iCODE)^56^
Physicians	

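### Repeated-measures ANOVA is the only method named for 4-week change in categorical primary outcomes; it does not fit unordered answers, has no stated site or country term, and leaves missed 4-week forms unclear

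*Protocol article*

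**What the plan says.** In the protocol article, Analysis plan, Primary outcomes, the outcomes are what patients and relatives experience, worry about, expect and prefer. They "will be described in frequencies and narrative descriptions", and "The proportion of patients who have certain concerns, expectations and preferences will be described". Score summaries are conditional: "Statistics on mean/median scores and variance will be presented where applicable". Table 2 (Measurements) gives the patient instrument as "Self-developed questions adapted from the Serious Illness Conversation Guide" and a second questionnaire, with no scale score stated.

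For change, the same section says "Repeated measures analyses of variance will be conducted to assess the development of outcomes between baseline and 4 weeks follow-up". No other method for change is given, and the Secondary outcomes section repeats the sentence.

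Multilevel modelling, with clustering at country level, is planned for associations with country and patient characteristics. Site is used only to tabulate baseline characteristics. The sentence after the ANOVA sentence plans multiple imputation by chained equations (MICE), on the ground that patients may leave questions unanswered. The Sample size section expects "30% of all patients who complete the baseline assessment will be lost to follow-up, due to death, significant deterioration of health or other causes".

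**The concern.** The method is stated, not left open, and it is a method for a continuous response applied to outcomes that the same section treats as categories. Three things follow.

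- **Scale.** On unordered or multi-category answers an F test on category codes tests nothing interpretable. On binary answers it yields a difference on the probability scale, whose size depends on the starting prevalence.
- **Clustering.** The ANOVA carries no stated term for site or country, although patients come from two to six sites in each of 11 countries.
- **Missing 4-week forms.** About three in ten patients are expected to have none, for reasons that include death and deterioration. The stated reason for imputation does not reach them.

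At stake is the reading of the 4-week data. Under Follow-up 1, the article says this questionnaire serves to assess change, and the Discussion counts change within subjects as a strength of the study.

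**Working it through.** **1. The plan's own figures.** The Sample size section says "The number of 200 patients per country enables us to estimate proportions with 95% Confidence Intervals (CIs) of approximately ±7" per cent. With p = 0.5 and n = 200: 1.96 × √(0.25/200) = 6.93%. Numbers at 4 weeks: 2200 × 0.70 = 1540, and 200 × 0.70 = 140 per country. Both reproduce. The expected number without a 4-week form is 2200 − 1540 = 660 (30%). The half-width at n = 140 is 8.3%. No effect size, power, correlation over time or intraclass correlation (ICC) is given for the change analysis, so there is nothing further to reproduce.

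**2. Unordered answers.** Code three unordered answers A = 1, B = 2, C = 3. Let a share q of patients move from A to B and an equal share q from C to B. The mean change is q(+1) + q(−1) = 0, so ANOVA sees no change although the share answering B has risen by 2q. Recode A = 1, C = 2, B = 3 and the same data give q(+2) + q(+1) = 3q. The result depends on arbitrary codes.

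**3. A single binary item.** With two time points, repeated-measures ANOVA is a paired t-test (F = t²). Simulated under no change, with an assumed within-patient correlation of 0.5, no clustering and no dropout (3000 runs each):

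| Prevalence | Type I error, n = 140 | Type I error, n = 1540 |
|---|---|---|
| 50% | 4.6% | 5.3% |
| 10% | 4.4% | 5.0% |
| 3% | 3.8% | 5.2% |

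The test itself is therefore close to its nominal 5%. The weakness is the effect scale: an odds ratio of 1.5 is a 4-point change from 10% (to 14.3%) and a 10-point change from 50% (to 60%). Comparing changes between subgroups with different starting levels then mixes the two.

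**4. Clustering of the change.** The Study design and setting section lists 20 hospitals, 7 palliative care institutes and 8 out-of-hospital settings, so 35 sites. Completers per site: 1540/35 = 44. Stable differences between sites cancel in within-patient change, so only the ICC of the change matters, and it is assumed here. Design effect = 1 + (44 − 1) × ICC; actual type I error = 2 × [1 − Φ(1.96/√design effect)].

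| Assumed ICC of change | Design effect | Actual type I error |
|---|---|---|
| 0.005 | 1.22 | 7.5% |
| 0.01 | 1.43 | 10% |
| 0.02 | 1.86 | 15% |
| 0.05 | 3.15 | 27% |

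This takes equal-sized sites and all pairs analysed as independent.

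**5. Missed 4-week forms.** If the analysis ended up in completers only, the error in a 4-week prevalence would be 0.30 × (prevalence in the lost − prevalence in completers). With completers at an assumed 40% and the lost at 50%, 60% or 70%, the completers' figure is 3, 6 or 9 points too low. This has meaning only for patients who are alive; the article does not split the 30% by cause.

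**The case against.** The strongest reply is that this is a mainly descriptive cohort. Its two aims are in-depth understanding and variability between groups, neither of which is change over time, and its sample size rests on the precision of proportions. The response formats of the self-developed questions are not given, so the number of unordered items is unknown, and the secondary scores suit ANOVA on scale. All of this stands. It limits the weight of the point but does not make the method fit the categorical items.

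A reader might also infer stronger faults, which the article does not support:

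- **That 660 patients are dropped from every change analysis.** MICE is planned in the very next sentence, and a complete-pairs analysis is nowhere stated. Nor is it documented that the lost are mainly the sickest. What stands is that the scope of MICE is unclear.
- **That the ANOVA contradicts the multilevel approach.** The multilevel sentence covers associations and the ANOVA sentence covers change. The gap is in the second analysis. ANOVA can carry country as a between-subject factor, but none is stated.
- **That about 63 patients per site enter the clustering calculation.** That is the baseline number (2200/35). A change analysis in completers has about 44.
- **That ANOVA is invalid for any binary item.** Step 3 shows near-nominal type I error in the simple case.
- **That ANOVA is prescribed for bereavement.** The Secondary outcomes sentence is limited to baseline and 4 weeks, and bereavement is collected 8–10 weeks after death, so it falls outside that wording.

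**Conclusion.** The point holds in a limited form and should be fixed before analysis; it does not undermine the study. Repeated-measures ANOVA is the only method named for change in the primary outcomes, and it is not meaningful for unordered answers. For binary answers the fault is the effect scale, not the bare test. The absence of a site or country term could raise type I error to about 7.5–27%, but that range rests wholly on assumed ICCs of 0.005–0.05 for the change and on equal sites of about 44 completers. How the expected 30% without a 4-week form are handled, and deaths among them, cannot be told from the text.

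**What to change.** In the Primary outcomes analysis, replace the ANOVA sentence. For change in categorical outcomes, name logistic mixed models for binary items and ordinal or multinomial mixed models for the others (or GEE), with time, patient and site effects and country as a fixed effect. For score outcomes, here and in the Secondary outcomes section, name linear mixed models with the same structure.

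State that all available observations from patients while alive are used, that answers are not imputed after death, and whether MICE extends to living patients who missed the 4-week form. Table 2 already lists patient survival as taken from medical files, so deaths can be told apart from other missing forms.

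Cost: a change of wording and slightly more modelling work. No new data are needed, and the sample size does not change.
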